## Abstract

**Background:**

Tuberculosis (TB) remains a significant public health challenge, particularly in rural areas of high-burden countries like China. Active case finding (ACF) and timely treatment have been proven effective in reducing TB prevalence, but the impact on the TB epidemic when employing new technologies in ACF is still unknown. This study aims to evaluate the effectiveness of a comprehensive ACF package utilizing mobile vans equipped with artificial intelligence (AI)-aided radiology and GeneXpert testing in reducing TB prevalence among high-risk populations in rural Guangxi, China.

**Methods:**

A pragmatic cluster randomized controlled trial will be conducted in two counties of Guangxi, China. The trial will randomize 23 townships to intervention or control groups at approximately 1:1 ratio. The intervention group will receive an ACF campaign in Year 1 among high-risk populations, incorporating visited by mobile vans equipped with AI-based digital X-ray screening, symptom assessment, and sputum collection for GeneXpert testing. Control group participants receive usual care. TB patients identified in Year 1 will complete their treatment in Year 2. The primary outcome is the prevalence rate of bacteriologically confirmed TB among high-risk populations in Year 3. Process evaluation will explore acceptability, feasibility and adaptation of the intervention. We will conduct incremental costing study to inform future scale-up of the intervention in other settings.

**Discussion:**

This study will provide valuable insights into the effectiveness and feasibility of utilizing AI-equipped mobile vans and GeneXpert for TB ACF to reduce TB prevalence in rural settings. If successful, this model will contribute to possible solutions to achieve the WHO End TB Strategy by 2035.

**Trial registration:**

ClinicalTrials.gov NCT06702774

## Introduction

The United Nations passed the Resolution to end tuberculosis (TB) by 2035. TB is the leading cause of death in infectious diseases. In 2022, the world reported 7.5 million new TB cases and 1.3 million deaths caused by TB [1]. TB incidence has declined by 2% a year between 2010 and 2020. However, the rate has reverted to increase by 3.9% between 2020 and 2022 due to the COVID-19 pandemic [1]. To reach the END-TB resolution, global TB incidence has to be reduced to less than 100 per million by 2035 [2]. The world is looking for evidence of innovative approaches to eliminate TB in a relatively short time frame [3].

The principle of “prevent, search, detect, treat” has successfully reduced TB prevalence in high-income countries in the 20^th^ century [4]. Studies in high TB burden countries also proved that active case finding (ACF) at the community level would identify patients who are in their early stage of disease development, or who may be delayed or missed in the routine passive case finding at health facilities [4,5]. A 2009 study in rural Zimbabwe showed both mobile van and household-to-household sputum collection methods lowered TB prevalence by 41% in three years, showing the potential of using mobile vans in case finding [6]. Another study in rural Vietnam demonstrated that conducting annual community-based screening using a rapid molecular diagnostic tool (GeneXpert) for three years could reduce 40% of TB prevalence in a high TB burden setting [7]. However, GeneXpert costs around US$15 per test, which is prohibitive to be used as a large-scale screening tool.

More cost-effective active case-finding tools, such as computer-aided diagnostic tools using artificial intelligence (AI) deep learning neural networks, have shown satisfying sensitivity (86%) as a screening tool to reduce 66% of cases needed for laboratory tests [8]. Operational studies revealed the feasibility and effectiveness of using AI-facilitated X-ray and GeneXpert for community screening and diagnosis [9]; however, most studies were pre-after comparisons that were not properly designed to evaluate epidemiological impacts [10]. In addition, two studies in Africa highlighted that the interventions were more cost-effective when screening elders, close contacts of active TB patients, and individuals with comorbidities such as diabetes and HIV [11,12].

In this study, we aim to implement and evaluate the feasibility and effectiveness of a comprehensive intervention package in rural Guangxi, China, a high TB prevalent setting, that employs the latest technologies for active case finding to reduce TB epidemics among high-risk populations. The new technologies include employing a mobile van equipped with AI-aided radiology screening and GeneXpert test for active case finding in communities. Our study is designed as a pragmatic clustered randomized controlled trial to evaluate the effectiveness of the comprehensive package in reducing TB prevalence over a period of three years among high-risk populations.

## Methods

This protocol is reported according to the Standard Protocol Items: Recommendations for Interventional Trials (SPIRIT) guidelines (see S1 File).

### Study status and timeline

The lifespan of this study will be 42 months in total, including 36 months for the main trial (Year 1–3). More details of the trial timeline are included in Fig 1. The trial started in November 2021 and was suspended for 3 months due to COVID-19 control in Year 1. Thus, the progress was postponed accordingly. Participant recruitment and data collection have been ongoing by the time of submission of this protocol, which are estimated to be completed by the end of January 2025. The trial results will be disseminated through research articles and policy briefs after the trial evaluation is completed after April 2025. We aim to publish our results and findings in leading international medical journals and present at national and international conferences.

**Fig 1 pone.0316073.g001:**
[figure not shown]
SPIRIT schedule of enrolment.

### Study design and setting

We will conduct a parallel two-group, cluster randomized controlled trial of a comprehensive package of active case finding followed by timely treatment in rural Guangxi China to evaluate whether the interventions could reduce the TB epidemic compared to the usual care (Fig 2). Guangxi is located in southwest China, bordering with Vietnam. Guangxi reported 31,913 TB cases with a notification rate of 70/100,000 in 2020 among all populations, representing the second highest TB burden in China. Of the reported TB cases, 74% were from rural areas, and 30% were elderly ( ≥ 65 years old). Mountainous areas in Guangxi had high TB notification rates; for example, the two trial counties (Xincheng and Xiangzhou of Laibin Prefecture) reported an average notification rate of 134/100,000, which is two times the provincial average. In addition, the Covid-19 pandemic has substantially delayed TB diagnosis and treatment, which would fuel up TB transmission and exacerbate the TB epidemic.

**Fig 2 pone.0316073.g002:**
[figure not shown]
Trial design flow chart.

TB services in China are publicly funded and delivered by different public facilities at the county, prefecture, province and national levels. The TB free treatment policy covers basic TB diagnosis tests and treatment for drug susceptible cases, while health insurance schemes cover treatment costs for drug resistant cases. The County Centre for Disease Control (CDC) is responsible for TB planning, reporting and quality control, while the County Hospital provides clinical care. Passive case finding is the practice of usual care, where patients with chronic cough or other TB-related symptoms are self-presented or referred to the County Hospital for diagnosis and treatment. TB diagnosis is based on sputum smear, chest X-ray examinations, and clinical assessments. Standard WHO DOTS treatment regimen is provided for drug-susceptible cases. TB patients visit the County Hospital monthly to renew their medications. Patients take their anti-TB medications daily with the support of village doctors, who are community health workers. In Guangxi, village doctors are semi-private. They receive 50% of income from the township hospitals for their public health work such as maternal and child health, immunization, pap smear screening, and disease management including TB, diabetes, and hypertension, while they earn the other 50% income from clinical consultations covered under the rural health insurance scheme. According to the National TB Guideline, village doctors are responsible for visiting TB patients weekly. The public health doctor in the township hospital is responsible for supervising village doctors and visiting patients monthly. However, the actual frequencies of both doctors are far less and often substituted via phone calls. In each village, there is a female social worker in the Village Committee, who plays a major role in public education, maternal and child care, and protecting women’s rights. These female social workers have a strong connection with villagers but have not been involved in TB care.

### Eligibility criteria

#### Clusters.

Township is treated as the cluster of intervention. A township is an administrative unit with a township hospital and consists of 7–12 villages. All townships in Xincheng and Xiangzhou county, which provide their willingness to participate, will be included. Villages within the participating township serve as sampling units in the epidemiological survey at Year 3 to determine the TB prevalence rate.

#### Participants.

In each township, all permanent residents based on household registration who are 15 or older and reside in the village or township at the time of investigation become eligible if meeting one of the following criteria as high-risk population: 1) elderly (i.e., aged 65 and above), or 2) aged below 65 but with one of the following conditions: being patients previously treated for TB, or close contacts of a patient with a TB patient diagnosed within the last three years; having been clinically diagnosed with diabetes, HIV positive, or worked as a miner. All eligible participants must sign informed consent forms to be recruited. Residents who refuse participation will be excluded.

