#### Usual care.

Usual care, i.e., the routine TB care provided in the National TB program, is provided in the control group, and no active case finding activities will be provided.

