#### Intervention.

In the intervention group, in addition to usual care, we will implement an ACF campaign among all eligible participants in Year 1 (Fig 3). Prior to the visit, village social workers and village doctors will conduct door-to-door visits to recruit participants and obtain their informed consent. We will drive the mobile van to the village, and equip an AI-facilitated digital radiography (DR) machine and refrigerator on the van on a mutually agreed date. On the day, all eligible participants will be invited to complete a brief questionnaire regarding basic demographic information, medical history, smoking status and TB related symptoms, and then are invited to have their DR examined in the van. Based on digital chest X-rays, the AI software will identify TB assumptive participants who may have active TB, suspected TB or healed TB. In the first month of implementation in each county, one township hospital radiologist will facilitate the X-ray examination, double-check all results of the AI software, and make the final recommendation for presumptive TB. This process will be recorded to adjust the threshold score used by AI in each county. After the first month, the township hospital radiologist will still accompany the mobile clinic to help evaluate X-ray results if AI suggests for other lung diseases such as pneumonia or lung cancer, to minimize the risk of missing possible TB cases. Those who are presumptive of TB based on either DR examination or TB-related symptoms, i.e., any chronic cough over two weeks, hemoptysis, fever, night sweats, chest pain or unexplained weight loss, will be asked to produce a single on-site sputum. These villagers are also asked to take two specimen boxes for the collection of night and morning sputum. All staff are trained for good quality sputum sample collection, storage and transportation. Medical nebulizer inhalation will be provided to those who can not provide good-quality sputum. Sputum samples, either collected on the day or delivered by village doctors within 48 hours, will be stored in the refrigerator on the mobile van and transported back to the County Hospital daily for sputum testings, including smear microscopy, culture and GeneXpert assay. We will employ a sample mixing approach which has been validated in our previous publication [13]. Bacteriologically confirmed TB is defined by a positive result from any of the above sputum tests based on WHO and China National TB Program guidelines. Participants who are bacteriologically negative but have abnormal X-ray result or TB symptoms are referred to the county hospital for clinical assessment by a panel committee consisting of three senior doctors based on China National TB guideline for the diagnosis of clinically confirmed TB. All diagnosed TB patients, either bacteriologically or clinically confirmed, will be notified by the village doctor within 48 hours and referred to the County Hospital for standard WHO DOTS regimens per national guidelines.

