### Outcomes

Our primary outcome indicator is the prevalence rate of bacteriologically confirmed TB in Year 3 among the high-risk populations, including those 65 and older, those who are under 65 but have a history of tuberculosis treatment or have been in close contact with a person diagnosed with TB within the past three years, have been clinically diagnosed with diabetes, HIV, or have a background of working as a miner. According to WHO definitions, bacteriologically confirmed case is defined as having a positive test from any of the three tests (i.e., GeneXpert, smear or culture). Prevalence is estimated using a cluster-random survey among the high-risk populations to be conducted in both the intervention and control groups in Year 3. The numerator is the bacteriologically confirmed TB cases identified from the Year 3 prevalence survey plus TB cases reported from the National TB program, and the denominator is the number of high-risk populations who are permanent residents and reside in the area at the time of the prevalence survey. The numbers of numerators and denominators at the village level will be aggregated at the township level and calculated based on the WHO TB prevalence survey analysis guide to estimate the TB prevalence rate in the intervention or control group [14].

There is a list of secondary outcome indicators, which allow us to assess and evaluate whether our interventions could bring positive impacts on TB epidemic between the intervention and control groups: 1) prevalence rate of active TB of the high-risk populations, including both bacteriologically confirmed and bacteriologically negative but clinically confirmed cases, among the high-risk populations in Year 3. This indicator will be calculated based on findings from the prevalence survey in Year 3 estimated using the WHO TB prevalence survey guideline [14]; 2) notification rates of bacteriologically confirmed TB cases among the whole population in Year 3; and 3) notification rates of active TB cases, including both bacteriologically confirmed and clinically confirmed cases among the whole population in Year 3. Numerators of the two notification rates will include TB cases identified from our prevalence survey in Year 3 plus TB cases reported from the National TB Program, while both denominators include all adult permanent residents (i.e., those of 15 years and older) who reside in the intervention and control groups at the time of prevalence survey.

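### Close contacts of cases found by the Year 1 campaign enter the Year 3 primary population in the intervention arm only

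*Protocol article*

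**What the plan says.** Participants (Eligibility criteria) admits everyone aged 65 and over. Below 65 it admits people with diabetes, HIV or mining work, and those qualifying by "being patients previously treated for TB, or close contacts of a patient with a TB patient diagnosed within the last three years". Residents "reside in the village or township at the time of investigation become eligible if meeting one of the following criteria", and no other date is given for judging risk status.

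Outcomes carries the same TB-dependent criteria into the primary outcome: people under 65 who "have a history of tuberculosis treatment or have been in close contact with a person diagnosed with TB within the past three years". It adds that "the denominator is the number of high-risk populations who are permanent residents and reside in the area at the time of the prevalence survey".

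The arms differ in Year 1. In intervention townships, "we will implement an ACF campaign among all eligible participants in Year 1" (Intervention). In control townships, "no active case finding activities will be provided" (Usual care). The Abstract states that "TB patients identified in Year 1 will complete their treatment in Year 2", so the treatment of campaign cases is over before the survey.

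**The concern.** Randomisation protects a comparison when the two analysis populations are defined by things that allocation cannot change. Age, diabetes, HIV and mining work meet that test for practical purposes. Recent contact with a diagnosed TB case does not, because the campaign exists to raise the number of diagnoses in one arm.

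Take two households with the same undetected case and the same healthy 40-year-old contact. In an intervention township the campaign finds the case, and at Year 3 the contact counts as high-risk. In a control township, if the case stays undiagnosed, the contact does not count. If such contacts have a different TB prevalence from the other high-risk residents, the odds ratio shifts for a reason unrelated to the effect of screening.

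The protocol's safeguards do not reach this. The limitations paragraph in the Discussion relies on randomisation for baseline balance, which cannot balance a group formed afterwards. The primary model works on township totals, and the secondary patient-level model adjusts for age, sex and ethnicity but not for risk category (Statistical analysis).

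**Working it through.** **Does the look-back cover the campaign?** Study status and timeline gives a November 2021 start, a three-month suspension in Year 1, and data collection ending by about the end of January 2025. A survey held at that last date looks back to the end of January 2022; a survey held earlier in Year 3 looks back further. Most or all Year 1 diagnoses therefore fall within three years of the survey.

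**Which criterion adds people?** The campaign screens only residents who already qualify. A campaign-detected case was therefore already high-risk, and so is the equivalent undetected person in a control township. Prior treatment mostly relabels such people; at most it keeps someone whose own contact window would have lapsed. The contact criterion is different, because a contact need not have qualified before.

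**The plan's own figure.** Inputs from Sample size: 300 versus 150 per 100,000, intra-class correlation 0.001, 500 eligible people per village, 80% power, p < 0.05 (taken as two-sided).

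- Per arm before clustering: (1.960 + 0.842)² × (0.003 × 0.997 + 0.0015 × 0.9985) / 0.0015² = 7.849 × 0.00448875 / 0.00000225, about 15,659. With pooled variance it is 15,662.
- Design effect: 1 + 499 × 0.001 = 1.499.
- 15,662 × 1.499 = 23,477 people; 23,477 / 500 = 46.95, so 47 villages.

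The stated 47 villages reproduce. The point concerns the definition, not the sample-size arithmetic.

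**Size of the effect.** The protocol gives neither the excess of diagnoses over control, nor the newly eligible contacts per case, nor the contacts' prevalence. I assume 150 to 600 extra diagnoses per 100,000 high-risk people (clinically confirmed cases also count as index cases), 1 to 4 new contacts per case, and a contact prevalence of 0 to 2,000 per 100,000.

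- People added per village: A = 500 × extra diagnoses × contacts per case.
- Share of the denominator: A / (500 + A).
- Observed ratio at the planned effect: [(500 × 0.0015 + A × contact prevalence) / (500 + A)] / 0.003, where the plan expects 0.50.
- With no true effect, 0.003 replaces 0.0015 and the ratio should be 1.
- Power: two-sided comparison of two proportions with 23,500 / 1.499 = 15,677 effective people per arm.

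Each range runs from contact prevalence 0 to 2,000 per 100,000.

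| Extra diagnoses per 100,000 | New contacts per case | Added per village | Share | Ratio (plan 0.50) | Ratio with no effect | Power |
|---|---|---|---|---|---|---|
| 150 | 1 | 0.75 | 0.15% | 0.499–0.509 | 0.999–1.008 | 0.80–0.78 |
| 300 | 2 | 3 | 0.60% | 0.497–0.537 | 0.994–1.034 | 0.81–0.73 |
| 600 | 4 | 12 | 2.34% | 0.488–0.645 | 0.977–1.133 | 0.82–0.48 |

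Example, middle row, upper end: (0.75 + 3 × 0.02) / 503 = 0.00161, and 0.00161 / 0.003 = 0.537.

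The sign changes where the contacts' prevalence equals that of the other intervention residents: 150 per 100,000 at the planned effect, 300 with no effect. Below that point the intervention is favoured; above it the ratio moves towards or beyond 1. With under one case expected per village at the planned effect (500 × 0.0015 = 0.75), a few added people can matter if their risk is high.

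**The case against.** The strongest objection is that the pool of new contacts is nearly empty. A newly eligible person must be 15 to 64, living in the village at the survey, and free of any other qualifying condition. The Discussion says most working-age residents are away for most of the year, and that those at home are mainly elders, who qualify anyway, and children; those under 15 are excluded. If there were 1.5 extra cases per village with 0.5 such contacts each, 0.75 people would join 500. Even at 1% prevalence, measured prevalence would be (0.75 + 0.0075) / 500.75 = 151.3 per 100,000, less than 1% above 150. This stands as a limit on size, and it makes the upper row of the table doubtful.

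Passive case finding also runs in both arms for three years, and control cases found that way bring in contacts too. Only the net excess matters. This also stands.

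It can further be said that the wording ties the survey date to residence rather than to risk status, and that sensitivity analyses belong in the analysis plan. But the protocol gives the three-year window no other anchor, and it fixes the outcome population itself.

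A reader might infer that treated campaign cases themselves swell the intervention arm while their control counterparts are left out. The documents do not support this, since those counterparts already qualify on other grounds. A reader might also infer that the bias most likely runs towards no effect, on the view that contacts carry more TB. No passage gives their prevalence.

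**Conclusion.** The point holds for the contact criterion. As written, the primary population is partly formed after randomisation by something the intervention changes, and neither randomisation nor the planned covariates correct it. The addition is probably small, and the range of roughly 0.15% to 2.3% of the intervention denominator rests on assumed yields and contacts per case. Out-migration and passive diagnoses in control townships could make it smaller.

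No direction can be asserted. A large distortion needs high values throughout. For instance, 4 extra diagnoses per village (800 per 100,000), 4 contacts each and 1% prevalence would raise measured prevalence by 18%: (0.75 + 0.16) / 516 / 0.0015 = 1.18. Nothing in the protocol supports that combination. This is a weakness of definition worth closing because it is cheap to close; it does not by itself undermine the trial.

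**What to change.** Keep screening everyone who is eligible at Year 3. For the primary analysis, exclude from numerator and denominator, in both arms alike, people under 65 whose only qualifying condition is TB treatment or contact arising from a diagnosis made on or after the start of the Year 1 campaign. Use one calendar date for both arms, and apply the same rule to the National TB Program cases that enter the numerator. Report the full surveyed population as a sensitivity analysis, and show risk-category composition by arm. Write this down before anyone sees outcomes by arm.

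Restricting the contact category to people who qualified at a pre-campaign date, while keeping the three-year look-back at Year 3, would not be an easy alternative: few such people would still be eligible and screened.

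The cost is modest. The 47 villages per group stay as they are. The contact category becomes small in both arms, and a small share of surveyed people leaves the primary set; the protocol does not allow that share to be calculated. Contact history is already collected (ACF activities), as are program cases in both arms over three years (Laboratory testing and clinical consultation). The protocol does not say that the date of the index diagnosis is recorded, so it must be added to the questionnaire or linked from the registry.
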